### Development of Prediction Model

To develop evidence-based guidelines for the prescription of prosthetic ankle-foot devices, the goal of this investigation is to determine which factors and outcomes are the most predictive of optimal performance to meet patient goals. To do this, initial analyses will consist of bivariate cross-tabulations, performed using chi-square analyses. Variable selection for the multivariate model will be informed by these bivariate findings. Logistic regression will then be performed with participants’ preference of prosthesis regressed on each of several domains (eg, functional levels and outcomes, activity levels, and biomechanical parameters). The models will simultaneously control for multiple variables, and overall model predictive value will be assessed using the C-statistic. Domain-specific models (based on bivariate findings) and 1 parsimonious stepwise logistic regression model combining the domains will be created to determine whether each distinct component predicts optimal prescription outcome. Each domain-specific model will control for the identified confounding factors. The individual variables of each domain will be used as fixed predictors. Finally, stepwise multiple regression will be used to determine the factors and outcomes that represent the best predictors, which will be conducted through a series of domain-specific, forward regression models. The significant variables in the forward selection models will then be placed in a backward regression model. Significant variables from the backward regression will be considered as the strongest predictive factors and used to develop prosthetic prescription guidelines.

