**6-Minute Walk Test (6MWT)**
6MWT measures the distance an individual can walk in 6 minutes without help or encouragement. The 6MWT is a valid and reliable metric that correlates with physical function and functional capacity [34] and has good interrater and intrarater reliability in individuals with lower limb loss [34].

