**Prosthesis Evaluation Questionnaire (PEQ)**
PEQ is self-report, visual analog scale–style questionnaire for individuals with lower limb loss who use a prosthesis. It is used to evaluate the prosthesis and life with the prosthesis. It consists of 82 items with 9 functional domain scales, including ambulation, residual limb health, utility, appearance, sounds, frustration, perceived response, social burden, and well-being. The PEQ also contains items beyond the subscales, including satisfaction, pain, transfers, prosthetic care, self-efficacy, and importance [42].

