### Data Analysis

The reflective marker positions will be digitized using motion tracking software. A 15-segment (head, trunk, pelvis, bilateral upper and lower arms, hands, thighs, shanks, and feet) rigid body model will be created based on the skin-mounted markers and functional joints. Local coordinate systems for each segment will be defined using the International Society of Biomechanics recommendations [52,53]. The data of acceptable walking trials of each participant at each speed will be processed using Visual3D. Marker data will be filtered with a 6-Hz Butterworth low-pass filter. Raw analog data will be filtered using a second-order low-pass Butterworth filter with a 25-Hz cutoff frequency. Visual3D will be used to calculate temporal-spatial values, walking speed, and lower extremity kinematics and kinetics. Inverse dynamic analysis will be applied to the kinematics of the biomechanical model and to the location, magnitude, and direction of ground reaction forces acting on the foot to calculate lower extremity joint torques and powers, including ankle, knee, and hip power of the biological and prosthetic limbs during stance and the frontal plane knee moments for the unaffected limb of participants (30/100, 30%). The resultant ground reaction force will be calculated as the magnitude of the ground reaction force vector. Several parameters, including temporal-spatial variables (eg, step lengths, stance and swing times, cadence, and stride length); peak angles; segment ranges of motion, moments, and powers for the ankles, knees, and hips during each phase of gait; and other biomechanical parameters (eg, external adduction moment rate, impulse external knee adduction moment, peak vertical ground reaction force, and peak resultant ground reaction force) will be measured and statistically compared across all conditions. Means, maximum and minimum values, ranges of motion, SEs, and coefficients of variation will be computed for the values attained per gait cycle over each trial and for each set of trials.

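### Chi-square cross-tabulation is the only bivariate screen named for the prescription model, although most candidate predictors are continuous and would have to be cut into categories

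*Protocol article*

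**What the plan says.** The section Development of Prediction Model sets out a sequence. First, "initial analyses will consist of bivariate cross-tabulations, performed using chi-square analyses". Next, "Variable selection for the multivariate model will be informed by these bivariate findings"; the domain-specific models are likewise said to rest on the bivariate results. Logistic regression follows, with participants' "preference of prosthesis regressed on each of several domains". The example domains are "functional levels and outcomes, activity levels, and biomechanical parameters". Forward and then backward selection yields the predictors from which the guidelines are to be written.

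The measures in those domains are described elsewhere in the article:

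- Walking: "6MWT measures the distance an individual can walk in 6 minutes without help or encouragement".
- Questionnaire: the PEQ is in visual-analog style, and "It consists of 82 items with 9 functional domain scales".
- Gait: the Data Analysis section lists "segment ranges of motion, moments, and powers for the ankles, knees, and hips during each phase of gait", and "lower extremity joint torques and powers, including ankle, knee, and hip power of the biological and prosthetic limbs during stance".
- Activity: step monitoring over 30 days, in the Visit 6 section.

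The prediction section gives no cut-points, no significance level for the bivariate step, no assumed preference split and no effect size. It names no bivariate method other than chi-square.

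**The concern.** A cross-tabulation needs categories, so a walk distance or a joint power can be used only after it has been cut. Two things are then lost: the differences between people within a category and, because Pearson chi-square treats categories as unordered, their ranking. The result also depends on where the cuts fall.

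The later logistic models can use the full scale, but only for variables carried forward. A measure that truly predicts preference may look unpromising in a cut-down table and be left out of the model that produces the guidelines. The gait measures are most exposed: they come from 30 participants, and a table of three categories by three devices would average 30/9 = 3.3 people per cell.

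This is a different problem from overfitting through repeated selection. It concerns real predictors missed at the first step.

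**Working it through.** **Stated figure.** None exists to reproduce. Table 2 gives power for differences between devices, not for the prediction model or its screen.

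**Inputs from the article.** There are 100 participants for functional and subjective measures and 30 for biomechanical measures. Alpha is 5% in the sample-size section (also .05 for the Friedman test); none is given for the screen.

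**Assumed inputs.** One third prefer a given device. The predictor is normal, and its mean differs by d SD between those who prefer the device and those who do not. The screen is two-sided at .05.

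**Closed-form check.** For the uncut predictor, the expected test statistic is d / √(1/n₁ + 1/n₂), and power ≈ Φ(statistic − 1.960). A median split has asymptotic efficiency 2/π = 0.637, so the statistic is multiplied by √0.637 = 0.798.

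- n = 100, d = 0.6: √(1/33.3 + 1/66.7) = 0.212, so the statistic is 2.83 and power is Φ(0.87) = 81%. After a median split: 2.83 × 0.798 = 2.26, and Φ(0.30) = 62%.
- From exactly 80% power, whatever the split: (1.960 + 0.842) × 0.798 − 1.960 = 0.276, and Φ(0.276) = 61%. The loss is 19 points.

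**Simulation, strict .05 screen.** 4,000 replicates per setting; likelihood-ratio test of the logistic slope on the uncut value against Pearson chi-square after cutting:

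| n | d | Uncut | Median split | Tertiles | Quartiles | Loss (points) |
|---|---|---|---|---|---|---|
| 100 | 0.5 | 65% | 45% | 43% | 40% | 20–25 |
| 100 | 0.6 | 81% | 61% | 60% | 58% | 20–23 |
| 100 | 0.8 | 96% | 84% | 85% | 82% | 11–14 |
| 30 | 1.0 | 72% | 50% | 46% | 41% | 22–31 |

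Repeat simulations agree closely: 78% uncut against 59/58/55% at n = 100, d = 0.6, and 71% against 51/45/40% and 68% against 48/45/41% at n = 30, d = 1.0. Null rejection at n = 100 was 5.6% uncut and 5.0–5.5% cut, so type I error does not explain the gap. At n = 30 it was 6.2% and 4.4–5.3%, which could explain 1 to 2 points.

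**Other preference codings.** With n = 100 and preference as a three-level outcome in equal thirds, power was 80% uncut against 61/58/54%. With a balanced binary preference it was 82% against 65/60/59%. An uneven cut at the 80th percentile costs more: 47% and 51% in those two settings.

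**Varying the screening level.** Here a predictor counts as found if it passes the chi-square screen and is then significant at .05 uncut. Loss in points against no screen, over median, tertile and quartile cuts (3,000 replicates, t-test as the uncut test):

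| n | d | Screen .05 | .10 | .20 | .25 |
|---|---|---|---|---|---|
| 100 | 0.6 | 22–26 | 12–16 | 5–6 | 3–4 |
| 100 | 0.8 | 12–14 | – | 2–3 | 1–2 |
| 30 | 1.0 | 22–30 | – | 4–6 | 3–4 |

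A repeat run put the loss at .20 to .25 at about 1 to 7 points. The screening level, which the article leaves open, drives the result more than d, n or the number of categories.

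**The case against.** The strongest reply is that the article does not describe a strict filter. Selection is only informed by the bivariate step, which is compatible with a generous threshold or with judgement alongside other evidence. The last table shows that a generous threshold leaves little loss. This stands, and it rules out any flat statement that the screen costs about 20 points of power.

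A second reply is that the article never says walk distance, PEQ scores or joint powers will be cross-tabulated. The example domains are attached to the logistic regression sentence, and many candidate factors (sex, race, etiology, employment, marital status) are properly categorical. A journal article may also leave the handling of continuous variables to the full plan. This stands in part: missing cut-points are no fault of the article. But the section seeks the factors and outcomes that best predict preference, describes the initial analyses as cross-tabulations without restriction, and bases the domain-specific models on them. Anyone following that text would have to cut the continuous measures. The point concerns a method that is stated, not a detail left out.

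A third reply is that one-variable screening followed by forward and backward selection is a larger weakness than the choice of test. That may be so, and changing the test does not cure it, but it does not make cutting the measures harmless.

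**Conclusion.** The point holds as a poor choice of screening method whose cost is conditional. If one third prefer a device and the screen is strict at .05, the loss is about 11 to 25 points at n = 100 for d of 0.5 to 0.8 (about 80% down to 55–61% at d = 0.6) and about 20 to 31 points at n = 30 for d = 1.0. With a screen at .20 to .25 and uncut models afterwards, it is about 1 to 7 points. These figures rest on assumed effect sizes, preference split, cuts and screening level, because the article supplies none of them.

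A reader might infer that a fixed share of power is lost, that every variable failing the screen is excluded, or that measures stay categorised in the logistic models. The article supports none of these: it sets no exclusion rule and does not say that the later models use cut values. What remains is that the only bivariate method named does not suit most of the measures it would be applied to, and that a better one is available at almost no cost.

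**What to change.** In Development of Prediction Model, restrict chi-square cross-tabulation to truly categorical factors such as sex, race, etiology and current foot type. For continuous and ordinal-scale measures, replace it with a one-predictor logistic regression of preference on the uncut measure (multinomial if preference is kept at three levels), adding a spline term where non-linearity is a concern. State that these measures stay uncut in the domain-specific and combined models.

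The cost is a few sentences and a small change of code, with no new data. The one small downside is having to check linearity. If the full plan already confines chi-square to categorical factors, a clarifying sentence is enough.

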#### Visits 3 to 5—Functional Assessment of ESR, ART, and PWR Ankle-Foot Devices

Visit 3 will begin after the 1-week acclimation period while using the first assigned ankle-foot device. Participants will complete the VAS pain scale and then a battery of outcome measures and surveys (outlined in the following sections). In addition, during visit 3, a subset of participants will also be randomized to undergo biomechanical gait analysis while using the first prosthesis (described in the following sections). Once visit 3 is completed, the participant will receive the second prosthesis according to the established randomization schedule, and the initial prosthesis will be returned to the study prosthetist. The participant will again complete a 1-week acclimation period. During visit 4, the participant will undergo the same pain scale and battery of outcome measures and surveys. The same subset of participants will also undergo biomechanical gait analysis using the second prosthesis. The third prosthesis will be issued at the end of visit 4, and the second prosthesis will be returned to the study prosthetist. Participants will receive the same 1-week acclimation and will complete the same pain scale and battery of outcome measures and surveys during visit 5. In addition, the same subset of participants will undergo biomechanical gait analysis while using the third prosthesis. For visits 3 to 5, a visit window of –2 to +2 days will be implemented.

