#### Functional and Subjective Outcome Measures

The functional and subjective outcome measures were selected to optimize relevance to the participant population, providers, and health care systems. These measures are commonly used in prosthetic clinics and represent critical information in the functional and subjective domains needed to develop guidelines for prescription. Following the completion of the investigation, the selected outcome measures will be statistically analyzed to determine which measures are the most sensitive to changes in device type. The battery of functional outcome measures and subjective surveys collected after each acclimation period will be administered by a local research team member. Functional outcome measures include the 6-Minute Walk Test, Timed-Up-and-Go, Four Square Step Test, Amputee Mobility Predictor, Stair Assessment Index, and Hill Assessment Index. Surveys include the Prosthesis Evaluation Questionnaire, Short Form-12, and Orthotics and Prosthetics Users Survey. These measures are described in Textbox 2.

Measures included in the study.

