#### Visit 6—Home-Based and Community-Based Assessment

After the completion of visits 1 to 5, participants will return home with all 3 prostheses for a period of 30 days, to assess performance and preference during home-based and community-based conditions. All 3 prostheses will be fitted with a Modus Health StepWatch 3 (Modus Health LLC), which is a research-grade instrument for long-term assessment of ambulatory activity during day-to-day life [45,46]. Capturing prosthetic performance while navigating home-based and community-based environments is a key piece of information that is yet to be effectively used in the prescription process [47]. Activity monitoring devices, such as the Modus Health StepWatch 3 used in this investigation, offer the potential to capture this critical information owing to their accuracy for those ambulating with a prosthesis [48]. Participants will also complete an activity log to document their daily activities to allow for correlation between the prosthesis used and activity. Participants are free to use each prosthesis as they choose. Ankle-foot device preference will be based upon total activity time for each prosthesis. Following 30 days of home-based and community-based use, participants will return to the prosthetic clinic to complete a closeout, guided interview to assess subjective preferences. A visit window of –5 to +5 days will be implemented for the final visit.

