#### Biomechanical Analysis

In addition to completing the functional and subjective outcome measures during visits 3 to 5, a subset of 30% (30/100) of the participants will also undergo gait analysis during these visits. Biomechanical gait analysis will include kinetic and kinematic evaluation of level ground walking at 3 speeds and kinematic evaluation of incline and decline ambulation at a self-selected speed. The purpose of these sessions is to collect joint angles, forces, torques, and powers while participants use each ankle-foot device.

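### The model for preference among three devices has no device-specific or within-participant structure, although its main predictors are measured once per device in every participant

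*Protocol article*

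**What the plan says.** Under Development of Prediction Model, the protocol article sets the goal to "determine which factors and outcomes are the most predictive of optimal performance to meet patient goals". The steps are bivariate chi-square cross-tabulations, then the model: "Logistic regression will then be performed with participants’ preference of prosthesis regressed on each of several domains". On the form of the predictors it says "The individual variables of each domain will be used as fixed predictors". Predictive value is judged by the C-statistic. Forward and then backward selection follows, and the surviving variables feed the prescription guideline.

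The data for this model are described elsewhere in the article:

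- **Outcome.** Under Visit 6, "participants will return home with all 3 prostheses for a period of 30 days", and "Ankle-foot device preference will be based upon total activity time for each prosthesis". Preference is therefore one choice among ESR, ART and PWR.
- **Functional and survey predictors.** These are taken at visits 3, 4 and 5, one device per visit: "The battery of functional outcome measures and subjective surveys collected after each acclimation period will be administered by a local research team member".
- **Gait predictors.** In the subset of 30, the sessions "collect joint angles, forces, torques, and powers while participants use each ankle-foot device".

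The Statistical Analysis section does rank devices within each participant and takes the mode. It also uses a Friedman test and a linear mixed model. None of these is tied to the preference model.

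**The concern.** For a measure taken on every device, the natural question for prescription is whether doing relatively better on a foot goes with choosing it. That is a comparison within a person. A participant who walks far on all three feet, or little on all three, says nothing about which foot suits them, yet such overall differences may make up most of the spread in the raw scores.

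The named tools are cross-tabulation, logistic regression with fixed predictors, and a C-statistic whose standard form is for a two-category outcome. None of them, as described, uses the matching of three scores to three alternatives. At stake is which variables survive selection: a measure that drives device choice through within-person differences could be dropped before it reaches the guideline.

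**Working it through.** The article gives no power or event count for the preference model, so there is no figure to reproduce. The check asks what each possible way of entering the three values can detect.

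**Inputs**

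- From the article: N=100 (30 for gait), three devices, alpha 0.05 (taken as two-sided), and the 6-minute walk row of Table 2, 60 (61) m.
- Assumed: 61 m is the SD of a between-device difference within a person, so the per-device SD is 61/√2 = 43.1 m.
- Assumed: between-person SD 43, 80 or 120 m in one set of runs, and 60, 100 or 150 m in another.
- Assumed: preference is reduced to one chosen device.

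**Model for the data**

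Score of person i on device j: X_ij = b_i + e_ij. Utility = β·X_ij + Gumbel noise, and the device with the highest utility is chosen. The term b_i is common to all three utilities and cancels, so only deviations from the person's own mean matter.

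**What each coding can see**

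- *Participant mean* (2 parameters). With independent, equal-variance errors, the mean is independent of the deviations, so it carries no information on the within-person effect.
- *One device's score* (2 parameters). Its correlation with that device's deviation is 43.1·√(2/3) / √(SD_b² + 43.1²) = 35.2 / √(SD_b² + 43.1²). This gives 0.58, 0.39 and 0.28 at SD_b = 43, 80 and 120 m.
- *All three scores, multinomial*: 2 equations × 3 scores = 6 parameters.
- *Two device differences, multinomial*: 2 × 2 = 4 parameters.
- *Stacked rows, unmatched logit*: 1 parameter. The between-person spread stays in the predictor, and each trio of rows holds exactly one chosen device, so the rows are dependent.
- *Conditional logit*: 1 parameter per measure.

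**Moderate effect, N=100**

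β = 0.4 per 43.1 m, which is 0.4/43.1 × 100 = 0.93 log-odds per 100 m. Power in % at between-person SD 43 / 80 / 120 m, 300 runs each:

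| Coding | Power |
|---|---|
| Multinomial, participant mean | 6 / 5 / 2 |
| Multinomial, PWR score | 19 / 14 / 7 |
| Binary PWR preferred, PWR score | 23 / 14 / 7 |
| Stacked unmatched logit | 62 / 16 / 1 |
| Multinomial, all three scores | 67 / 66 / 62 |
| Conditional logit | 89 / 88 / 86 |

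With no effect, the conditional logit rejected in 3-6% of runs and the stacked logit in 0-1%, against a nominal 5%. In a separate run of this setting, a multinomial model on two device differences reached 69-71%. With a somewhat larger effect, the conditional logit reached 96-98%, all three scores 81-84%, one device's score 11-29% and the mean 4-6%. A further run gave 97-99% for the conditional logit, 82-84% for all three scores and 87-90% for differences.

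**Large effect, N=100**

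1.5 log-odds per 100 m, between-person SD 60 / 100 / 150 m, 400 runs each:

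- Participant mean: the test rejected in 5.0-6.2% of runs.
- Stacked rows: the coefficient fell from 1.5 to 0.48 / 0.22 / 0.10, with rejection in 91.5 / 37.2 / 0.5%.
- All three scores: 97.0-97.8%.
- Conditional logit: 99.5-100%, mean coefficient 1.53-1.56.

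**Opposite scenario**

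Here overall fitness alone favours PWR (1.0 log-odds per 100 m) and relative performance has no effect. The participant-mean models rejected in 60.5-100% of runs, all three scores in 45.5-100%, stacked rows in 0-0.2%, and the conditional logit in 3.5-5.8%. The overall test on three scores therefore detects both effects without separating them.

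**Loss from the multinomial codings that keep the information**

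All three scores against conditional logit: 89−67, 88−66 and 86−62 give 22-24 points at the smallest effect tried; 98−84, 96−83 and 96−81 give 13-15 points at the next; about 2-3 points at the large effect. Device differences lost somewhat less.

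**The case against.** A reader might infer that the plan fixes an ordinary logistic model, whose test asks whether fitter people choose a given foot. The article does not support that. It says only logistic regression; multinomial and conditional logit belong to that family, and the article does not fix how the three values enter. The fitter-people reading holds only for codings with one value per participant. Stacked rows ask the within-person question badly, and three scores or device differences carry the information. A full analysis plan, not shown here, may settle the layout.

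A reader might also infer that finding out which kind of person likes which foot is off target. It is not: Study Objectives asks for criteria based on patient needs, goals and physical abilities. Participant-level factors are proper predictors and are known before any device is tried, whereas a device-specific score requires the patient to have used that device.

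The simulations generate choices from the same form as the conditional logit, which favours it. The 61 m is also uncertain: Table 2 heads its column as a difference, while the text above it speaks of within-group SDs, and the 96.3% power for this row is matched by a two-sample t test at 30 per group, not by a paired formula.

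All of this stands and limits the claim. What remains is that the article does name a screening test, a model family and a performance measure for this outcome, and none of them, nor the ranking under Statistical Analysis, brings a matched structure into the preference model.

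**Conclusion.** The point holds as a conditional one. The method as described has no device-specific or within-participant structure for a three-way choice with three-fold measured predictors, and the consequence depends on the coding:

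- **One value per participant:** nearly blind to relative performance, about 2-6% power for the mean and 7-29% for one device's score at moderate effects, against 86-99% for a conditional logit.
- **Stacked rows:** attenuated coefficient and wrong test size. The damage grows with the between-person spread.
- **All three scores or device differences, multinomial:** information kept, but roughly 10-20 points of power lost at moderate effects (slightly more at the smallest effect tried) and little at large ones.

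The conditional logit did at least as well as every alternative in these runs. The exact percentages rest on assumed effect sizes and between-person SDs, and on reading 61 m as a within-person difference SD. The ordering of the one-value codings against the conditional logit did not depend on which assumed value was used. The article does not show that the weakest coding will be used, so this is a change that should be made, not proof that the planned analysis must fail.

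**What to change.** In Development of Prediction Model:

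1. For predictors measured on each device, specify a conditional (alternative-specific) logit: three rows per participant, participant as the stratum, device intercepts, and one coefficient per measure.
2. Keep participant-level factors (etiology, time since limb loss, functional level) in the same model as interactions with device, so that the aim of patient-specific criteria is still served.
3. Replace the chi-square screen of these predictors with the single-variable version of this model, keeping the measures continuous.
4. Report within-participant concordance, meaning how often the chosen device is ranked first, in place of the ordinary C-statistic.

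The cost is plan wording and standard software, with no new data or visits. The downside is a performance measure that clinicians know less well.
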